## Abstract

The Break4Brain project aims to elucidate the effects of both acute and chronic physical activity (PA) on educational achievement in children with and without Attention Deficit Hyperactivity Disorder (ADHD). This study will be conducted in two phases: a cross-over design followed by a hybrid type 1 implementation-effectiveness trial, which includes both a cluster randomized controlled trial (RCT) and a qualitative study. In phase I, 60 children aged 10–12, with 30 each from ADHD and non-ADHD groups, will participate in a laboratory-based study over 4 days within 1 month. They will participate in three counterbalanced experimental conditions: (i) PA with cognitive engagement, (ii) PA without cognitive engagement, and (iii) a cognitively engaging control. This phase will assess acute changes in brain function, academic performance, working memory, inhibitory control, and sustained attention. Phase II will involve 600 children aged 10–12, randomly assigned to either a video-based PA program or a control group (300 children per group) in an 8-week cluster RCT. This phase will also incorporate a qualitative approach to explore the implementation context through pre- and post-intervention semi-structured interviews with teachers and school staff, and questionnaires for students. The outcomes of interest in this phase will include working memory, cognitive flexibility, selective attention, and academic performance. For the cross-over study, we hypothesize that PA conditions will enhance the studied outcomes compared to the control condition. In the RCT, we anticipate that the 8-week active breaks program will result in significant improvements in the selected outcomes compared to the control group. This study is expected to make pioneering contributions by including novel variables and focusing on the ADHD population. Furthermore, if the cluster RCT proves effective, it could offer a practical and cost-effective resource for integrating active breaks into daily school routines.

## Background

1

Physical inactivity and sedentary behavior pose a global challenge, impacting not only the physical health of youth but also exerting substantial implications on their brain health (Bull et al., 2020; Guthold et al., 2020). Over the past two decades, a wealth of evidence has accumulated, indicating that physical activity (PA) is among the most promising and cost-effective strategies for improving neurocognitive function (Morales et al., 2024). Thus, promoting PA during youth development can help to enhance the likelihood of academic performance, with childhood representing a particularly crucial stage (Álvarez-Bueno et al., 2017; Lubans et al., 2016; Singh et al., 2019; de Greeff et al., 2018; Muntaner-Mas et al., 2024). Altogether, the available evidence suggests a favorable effect size (small to moderate) of both chronic and acute PA on improving various domains of educational achievement, including brain function, cognition, and academic performance (Li et al., 2017; Sibbick et al., 2022).

Researchers have examined a wide variety of educational outcomes following acute PA in children without a neurodevelopmental disorder. Specifically, some systematic reviews and metanalytic studies shed light on the field and quantified the effect sizes of acute PA. In short, results of the Watson et al. (2017) meta-analyses showed that acute PA had a positive effect on improving on-task and reducing off-task classroom behavior [standardized mean difference = 0.60 (95% CI: 0.20, 1.00)], and this fact led to improvements in academic achievement [standardized mean difference = 1.03 (95% CI: 0.22, 1.84)]. Other reviews conclude that the effects of acute PA on the working memory and cognitive flexibility domains in children are inconclusive and scarce (Pontifex et al., 2019; Paschen et al., 2019). A recent meta-analysis by de Greeff et al. (2018) reviewed studies of children, 6–12 years old, that assessed the effect of single bouts of PA on inhibition. A small to moderate positive effect of acute PA was observed (Hedges’ *g* = 0.28, 95% CI = 0.01–0.56, *p* = 0.042). Similarly, investigations of selective and sustained attention have generally observed facilitations in the ability to focus and maintain attention following acute bouts of PA in children (effect sizes ranging from 0.1 to 0.69; Pontifex et al., 2019). In conclusion, the acute effect of PA in children without a neurodevelopmental disorder seems to exert a small but positive effect on educational outcomes.

Acute PA holds also notable benefits for children with cognitive impairments like Attention Deficit Hyperactivity Disorder (ADHD), a prevalent developmental disorder affecting 5.9% of youth globally (Faraone et al., 2021). ADHD symptoms include inattention, impulsivity, and hyperactivity, leading to academic struggles and deficits in multiple cognitive domains such as working memory and inhibitory control (Harrison et al., 2019). While ADHD medication helps manage some symptoms, it does not address learning disorders and executive function deficits effectively (Faraone et al., 2015). Despite several investigations that have examined the effects of acute PA in children with ADHD the exact nature of the response on brain function, cognition, and academic performance is still uncertain. To the best of our knowledge, there is no research examining the effects of acute PA on academic performance in children with ADHD. However, acute PA have been found to elicit transient benefits for overall cognitive performance in children with ADHD (Grassmann et al., 2017; Halperin et al., 2014; Li et al., 2023; Suarez-Manzano et al., 2018; Zhu et al., 2023). Specifically, a meta-analysis suggested that acute PA significantly benefit performance on inhibition, working memory, cognitive flexibility, and attention (Pontifex et al., 2019). This primer review on the topic also concludes that exist potential moderators of effects on cognitive functions related to the specified PA parameters intensity, duration, and volume in children with ADHD. While moderate-intensity aerobic exercise has shown promising results in improving ADHD symptoms and executive functions, research on the potential effects of other PA types, durations, and intensities remains largely unknown (Chan et al., 2022; Yu et al., 2020).

Additionally, recent systematic reviews have underlined the importance of evaluating the impacts of acute PA with low and high cognitive demands on cognitive performance (Paschen et al., 2019; Skulmowski, 2024). Some authors suggest that PA with cognitive engagement incorporates added stimuli, leading to heightened physiological arousal, thereby enhancing executive functions (Tomporowski et al., 2015; Best, 2010). In this regard, PA with cognitive engagement has demonstrated superior and longer-lasting effects on executive functions and ADHD symptoms in children with ADHD (Nejati and Derakhshan, 2021). Nonetheless, findings from other studies contradict this hypothesis, suggesting that PA with cognitive engagement do not necessarily enhance cognitive performance compared to bouts of PA without cognitive engagement or sedentary activities (Bedard et al., 2021). Thus, the current evidence on the effects of PA, as short bursts, and the cognitive demands of such activity in subsequent cognitive function remains elusive.

School environments offer an ideal setting to enhance children’s educational achievement through PA, benefiting both those with and without neurodevelopmental disorders (Howie and Pate, 2012). Specifically, integrating short bursts of PA, known as active breaks, during school time has been suggested as a valuable and feasible strategy in schools settings (World Health Organization, 2024). Active breaks typically last 3–15 min and are led by teachers to enhance learning outcomes, increase daily PA and reduce sedentary time. Examples of programs are TAKE 10! (Stewart et al., 2004), Energizers (Mahar et al., 2006), Transform-US Active Break (TAB) (Lander et al., 2024), and Burn2Learn (Mavillidi et al., 2021). On the one hand, the overall results of these programs have shown promising results of active breaks on brain function, cognition, and academic performance. However, scientific reviews have yielded mixed results, attributing certain differences to the quality and design characteristics of each program (Watson et al., 2017; Daly-Smith et al., 2018; Peiris et al., 2022). Overall, while scientific progress has been made in the field, the ideal dosage of active breaks for improving educational outcomes remains uncertain.

In this context, there is limited research substantiating the adoption, implementation, and sustainability of interventions under real-world conditions (Reis et al., 2016; Wiltsey Stirman et al., 2012), such as school settings. In this scenario, implementation models, such as the Reach, Effectiveness, Adoption, Implementation, and Maintenance (RE-AIM) framework, have been devised to evaluate the public health impact of interventions (Glasgow et al., 1999). School-based PA interventions demand a comprehensive grasp of the educational system, where contextual elements—such as organizational dynamics, intervention stakeholders, and the target population—operate with greater variability compared to the controlled settings typically found in research designs (Wolfenden et al., 2022). Qualitative approaches have been justified as a valid method to develop effective interventions through the examination of facilitators and barriers by the educational agents involved (Chalkley et al., 2018; Lane et al., 2022). Nonetheless, the extant evidence indicates limited consideration of this methodology in school interventions (Gelman et al., 2023; Koorts et al., 2022).

Therefore, exploring the optimal dose of PA, particularly through classroom-based active breaks, is vital for understanding its effectiveness in children with and without ADHD. Identifying this optimal dose is crucial for maximizing the impact on academic performance, cognition, and brain function across both populations. However, a significant gap persists in the literature, especially regarding the effects of large-scale active break programs in school settings. Moreover, implementing such interventions in school settings demands a multifaceted approach, involving collaboration among teachers, school staff, and students (Daly-Smith et al., 2021).

The primary aim of this study is to present the rationale, design, and methods of the Break4Brain Project. This project will investigate: (i) the acute effects of three experimental conditions— PA with cognitive engagement, PA without cognitive engagement, and a cognitively engaging control—on academic performance, cognitive function, and brain function in children aged 10–12, both with and without ADHD, using a cross-over design in a laboratory; and (ii) the chronic effects of two experimental conditions—a video-based PA program and a control condition—on academic performance and cognitive function in school-aged children (10–12 years old) within a school setting, utilizing a cluster RCT. Additionally, it will incorporate a qualitative approach to assess the feasibility of implementing PA initiatives in school settings and will include cost-effectiveness analyses.

## Methods

2

### Study design

2.1

The Break4Brain project will consist of two distinct phases: phase I will employ a cross-over design (ClinicalTrials.gov identifier: NCT06303674), while phase II will utilize a hybrid type 1 implementation-effectiveness trial (ClinicalTrials.gov identifier: NCT06319833). In phase II, we will implement a type 1 hybrid trial in primary schools across the Balearic Islands (Spain; Curran et al., 2012). The primary goal of this hybrid trial is to evaluate the effectiveness of the cluster RCT. Additionally, the secondary goal aims to better understand the implementation context through a qualitative approach. The qualitative component of phase II will be developed using the most comprehensive theoretical framework available in the literature (Yoshida et al., 2020). The project has been approved by the Ethics Committee of the University of the Balearic Islands (Ref No: 301CER22 for Phase I; and Ref No: 348CER23 for Phase II). Measurement protocols of each phase have been published in Zenodo.^1^ A SPIRIT schedule and overview of the study design can be found in Tables 1A, 1B. This protocol has been developed following the Standard Protocol Items: Recommendations for Interventional Trials (SPIRIT) checklist (Supplementary File S1). This research adheres to the guidelines outlined in the Declaration of Helsinki across all its facets. Before participation, explicit written consent will be obtained from both the school staff (phase II) and parents (phase I and II), and the participants’ assent will be also sought. Any modifications to the research protocol will be transparently communicated and duly registered on ClinicalTrials.gov, ensuring accountability and compliance with ethical standards.

**Table 1A tab1:** SPIRIT schedule of enrolment, interventions, and assessments of phase I.

	Enrolment	Allocation	Post-allocation			
Timepoint	*T1*	0	*T1 (baseline)*	*T2*	*T3*	*T4*
Enrolment						
Eligibility screen	X					
Informed consent	X					
Allocation		X				
Experimental conditions						
Cognitively engaging control				X	X	X
PA with cognitive engagement				X	X	X
PA without cognitive engagement				X	X	X
Assessments						
Brain function						
Event-related brain potentials – P3			X	X	X	X
Cognitive function						
Working memory			X	X	X	X
Inhibition			X	X	X	X
Sustained attention			X	X	X	X
Academic performance						
Academic fluency (Woodcock Muñoz^™^)			X	X	X	X
Verbal and non-verbal intelligence						
Kaufman Brief Intelligence test			X			
Physical activity patterns						
ActiGraph wGT3x-BT (21 days)						
Sedentarism patterns						
Youth Activity Profile-Spain			X			
Intensity of the active breaks						
Accelerometry (ActiGraph wGT3x-BT)				X	X	X
Heart rate monitor (Polar H10)				X	X	X
Sleep quality						
ActiGraph wGT3x-BT (21 days)						
Body composition						
Height			X			
Weight			X			
Waist circumference			X			
Hip circumference			X			
Biological maturation						
Peak height velocity			X			
Velocity of peak height growth			X			
Physical fitness						
Standing long jump test			X			
3-min step test			X			
Handgrip strenght			X			
4×10 shuttle run test			X			
Motor proficiency						
Short-form of Bruininks-Oseretsky Test of Motor Proficiency 2			X			
Mental health difficulties						
Strenght and Difficulties Questionnaire			X			
ADHD symptons						
ADHD Rating Scale-IV			X			
School grades						
Academic records			X			
Sociodemographic characteristics						
Family Affluence Scale II			X			
Parental education and occupation level						
*Ad hoc* questionnaire			X			

PA, physical activity; ADHD, Attention deficit-hyperactivity disorder.

**Table 1B tab2:** SPIRIT schedule of enrollment, interventions, and assessments of phase II.

	Enrolment	Allocation	Post-allocation			
Timepoint	*T1*	0	T1	T2	T3	T4
Enrolment				Baseline visit	Post 8-week intervention	
Eligibility screen	X					
Informed consent	X					
Allocation		X				
Interventions						
Video-based PA program						
Control condition						
Assessments						
Design and feasibility of active breaks						
Semi-structured questionnaire (students)			X			X
Semi-structured interviews (teachers)			X			X
Semi-structured interviews (school staff)			X			X
Implementation strategies						
Professional training			X			
Direct support						
Access to Break4Brain website						
Fidelity and follow-up of the active breaks						
Cognitive function						
Working memory				X	X	
Cognitive flexibility				X	X	
Selective attention				X	X	
Academic performance						
Academic fluency (Woodcock Muñoz^™^)				X	X	
Physical activity patterns						
The Physical Activity Questionnairefor Older Children (PAQ-C) a				X	X	
Sedentarism patterns						
Youth Activity Profile-Spain				X	X	
Intensity of the active breaks						
Accelerometry (ActiGraph wGT3x-BT)				X	X	
Body composition						
Height				X	X	
Weight				X	X	
Physical fitness						
International Fitness Scale				X	X	
Students classroom behavior						
Child and Adolescent Behavior Inventory				X	X	
Mental health difficulties						
Strength and Difficulties Questionnaire				X	X	
Creativity						
Adaptation of the Alternative Uses Task				X	X	
Sociodemographic characteristics						
Family Affluence Scale II				X	X	

PA, physical activity.

In phase I (Figure 1), measurements will be conducted in laboratory settings. Each participant will undergo all experimental conditions, with the order of conditions balanced and outcomes assessed after each. Overall, participants will participate in three experimental conditions (cognitively engaging control, PA with cognitive engagement, and PA without cognitive engagement). Each participant will undergo outcome assessments four times (once at baseline, and three times post each experimental condition), with a seven-day gap between each measurement day (as well-known as washout period, enough to avoid carryover effects; Li et al., 2015). Baseline assessment will take place on the first day without engaging in any experimental conditions.

**Figure 1 fig1:**
[figure not shown]
Study design and sample size for phase I (cross-over study).

Concerning phase II (Figure 2A), measurements will be carried out in school settings. Participating schools will be randomly assigned to one of two experimental conditions (control: usual academic lessons; intervention: video-based PA program [physically active without cognitive engagement]). The intervention will take 8 weeks, with the intervention condition implemented daily during this period. To design the experimental condition, a qualitative design will be conducted (Figure 2B).

**Figure 2 fig2:**
[figure not shown]
Study design for phase II (hybrid type 1 implementation-effectiveness trial: panel **(A)** - cluster randomized controlled trial; panel **(B)** - qualitative study).

### Participants and eligibility criteria

2.2

Children aged 10–12 will be recruited for phase I through the dissemination conducted in schools, hospitals, media, and social networks across Majorca (Balearic Islands, Spain). For phase II, recruitment will be focused on children of the same age (10–12 years) from Majorca, Ibiza, and Menorca (Balearic Islands, Spain) using the same dissemination methods.

The age group selection (in both phases) will be based on late childhood’s critical brain development stage, sensitive to maturation (Giedd et al., 1999; Johnson et al., 2009). We will select preadolescents over pubertal participants to avoid the varied changes that occur during puberty, which can interefere the investigation. Our phase I focus on ADHD stems from its childhood onset and lifelong persistence, often accompanied by comorbidities (Sayal et al., 2018). Early ADHD symptom and comorbidity management is crucial, with PA suggested to alleviate adverse effects, including cognitive impairment (Halperin et al., 2014; Hoza et al., 2016). The qualitative section of phase II will involve the participation of students from the class group, teachers, and staff members of the schools. This approach will ensure feedback from the three key stakeholders essential for the successful implementation of a PA intervention in schools based on the RE-AIM framework (Yoshida et al., 2020; Kennedy et al., 2021), and complemented by Daly-Smith et al.’s guidelines (Daly-Smith et al., 2021).

The specific eligibility criteria for each phase are detailed below:

• Phase I- (i) Children (10–12 years) diagnosed with ADHD by a psychiatrist, a psychologist or a pediatrician using the criteria of the Diagnostic and Statical Manual of Mental Disorders (DSM-5) without physical impairment; and (ii) Children (aged 10–12 years) without any neurodevelopmental or physical impairment.• Phase II- *Quantitative section:* (i) Children (10–12 years) without physical impairments.- *Qualitative section:* (i) Children (10–12 years) participating in the study; (ii) Teachers of the class that will participate in the study; and (iii) School staff from a participating school.

### Phase I: laboratory settings

2.3

#### Sample size and power

2.3.1

A within-subjects, 3 conditions (cognitively engaging control, PA with cognitive engagement, and PA without cognitive engagement) × 4 times (baseline, posttest 1, posttest 2, and posttest 3) repeated measures ANOVA design with 15 participants should be sufficiently powered to detect interactions at or above moderate effect sizes *f* = 0.25 which translates to an approximate Cohen’s *d* = 0.5 assuming alpha at 0.05, power at 80%, and a correlation among 4 repeated measures of 0.75. Considering the primer of Pontifex et al. (2019), the median sample size utilized within the literature investigating acute effects of acute bouts of PA on cognition has been below 15 participants. Considering this together, and a potential dropout rate of 10% observed in similar studies (Mora-Gonzalez et al., 2019), our investigation will recruit 30 participants with ADHD and 30 without ADHD.

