###### Cognition

2.3.4.2.2

A cognitive test battery covered by working memory, inhibition, and sustained attention will be administered to assess cognitive functions. All the instruments included in the study have undergone prior validation for use with the child population and cover the majority of cognitive domains affected by ADHD disorder (Wade et al., 2020).

####### Working memory

2.3.4.2.2.1

The computerized n-back test will be utilized to evaluate the ability to update information in working memory, a component of executive control (Jacola et al., 2014). Participants will be presented with a sequence of stimuli, in this case fruits, and will need to determine if each stimulus matches the one presented ‘n’ items ago (Supplementary Figure S2). Each of the 336 trials will start with the presentation of a central fixation point, followed by an Inter-Trial Interval (ITI) lasting a maximum of 2,500 ms (varies depending on response time). Stimuli will then promptly appear after the ITI and remain on the screen for 500 ms. The n-back test will be built in Opensesame stimuli presentation software (Mathôt et al., 2012). The median reliability coefficient alpha for this task in children population ranges 0.60–0.80.

####### Inhibition

2.3.4.2.2.2

The computerized flanker test will be used to assess the capacity to inhibit irrelevant stimuli within executive control (Krueger et al., 2009). The test is designed to measure the effect of irrelevant stimuli on cognitive processes. Specifically, participants are tasked with identifying the direction in which a central stimulus (in this case, fishes) is pointing, while simultaneously inhibiting the influence of surrounding distractor stimuli (fishes) (Supplementary Figure S3). Each of the 180 trials will begin with the presentation of a central fixation point, followed by an ITI lasting 1,100 ms, 1,300 ms, or 1,500 ms (variable time). Stimuli will then promptly appear after the ITI and will remain on the screen until the participant responds or up to 3,000 ms. The flanker test will be built in Opensesame stimuli presentation software (Mathôt et al., 2012). The Cronbach’s alpha for the flanker task in children typically falls in the range of 0.70–0.85.

####### Sustained attention

2.3.4.2.2.3

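### The Phase I power statement (15 participants, 80% power for 3 × 4 interactions) belongs to a different test, describes a layout the cross-over does not have, and omits the ADHD factor

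*Protocol article*

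**What the plan says.** Section 2.3.1 (Sample size and power, Phase I) describes a within-subjects repeated-measures ANOVA with three conditions and "4 times (baseline, posttest 1, posttest 2, and posttest 3". It states that this "repeated measures ANOVA design with 15 participants should be sufficiently powered to detect interactions at or above moderate effect sizes". The effect size is given as an f of 0.25, equated with a Cohen's d of 0.5; alpha is 0.05 and power 80%. The dependence between assessments is set by "a correlation among 4 repeated measures of 0.75". It then refers to the sample sizes usual in the literature and to "a potential dropout rate of 10% observed in similar studies", and concludes that "our investigation will recruit 30 participants with ADHD and 30 without ADHD".

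Three other places bear on this:

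- Sections 2.1 and 2.3.4 give each child four assessments seven days apart: one at baseline without any condition, and one after each of the three conditions.
- Section 2.3.5 (Data analysis) fits condition, time, group (ADHD or not) and the three-way interaction of condition, group and time.
- The Discussion presents the comparison of children with and without ADHD as a strength of the study and as a gap in the literature.

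**The concern.** This is the only power figure for Phase I, and three things about it do not fit the trial.

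- It names a condition-by-time interaction within children. Each post-test belongs to exactly one condition, so a child fills four cells, not twelve.
- It attaches the number 15 to an interaction test, and 15 does not appear to be the answer for that test.
- It contains no group factor, although the sample is two groups of 30 and the model tests group terms.

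At stake is what can be said when the results are in. Someone reading a null ADHD-by-condition result has no figure in the protocol by which to judge it. The translation of f = 0.25 into d = 0.5 could also lead that reader to think a half-SD difference between groups was covered.

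**Working it through.** **Inputs.** From section 2.3.1: f = 0.25 (f² = 0.0625), alpha 0.05, ρ = 0.75, 30+30 recruited, 10% loss (30 × 0.9 = 27 per group). Sphericity is not mentioned in the article; it is assumed throughout.

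**Formula.** For total N, k groups and m repeated measures, λ = f²·N·m/(1−ρ), referred to a noncentral F with df2 = (N−k)(m−1). For a within-factor effect df1 = m−1; for a group × within interaction df1 = (k−1)(m−1).

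**Step 1: where 15 comes from.**

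- One group, three levels, within-factor effect: λ = 0.0625×15×3/0.25 = 11.25, df 2 and 28, power 0.819. N = 14 gives 0.787, so 15 is the smallest N.
- Three groups, four measures, within-factor effect: λ = 0.0625×15×4/0.25 = 15, df 3 and 36, power 0.883. With N a multiple of three, 12 gives 0.778, so 15 is again the answer.
- One group, four levels, within-factor effect: 13 is enough (0.828).

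The article's 15 is thus reproduced in two standard ways. Both test a within-factor effect, and the second treats the three cross-over conditions as independent groups.

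**Step 2: the interaction named.** With conditions as groups, the 3 × 4 interaction at N = 15 has λ = 15, df 6 and 36, and power 0.765. N = 16 gives 0.802; the first balanced size is 18 (0.861).

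A fully within-child 3 × 4 interaction would have twelve cells. Then λ = 0.0625×N×12/0.25 with df 6 and 6(N−1), and 6 children would suffice (0.834). Counting four measurements instead of twelve cells in λ gives 0.810 at 15 and 0.775 at 14, but that is not the noncentrality of a twelve-cell layout, and children assessed four times cannot supply such a layout.

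**Step 3: condition × group, which the article does not calculate.** Let D be the ADHD-minus-non-ADHD difference in each condition, in SD units, relative to control. After group and condition main effects are removed, f² = ¼ × the variance of D over conditions (divisor m).

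| Pattern of D | f | λ at 60 / 54 | Power at 30+30 | Power at 27+27 |
|---|---|---|---|---|
| Omnibus, 0, 0.5, 0.5 | 0.118 | 10.0 / 9.0 | 0.805 | 0.758 |
| Omnibus, 0, 0.25, 0.5 | 0.102 | 7.5 / 6.75 | 0.676 | 0.625 |
| Single contrast, 0, 0.5 | 0.125 | 7.5 / 6.75 | 0.768 | 0.722 |

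At f = 0.25 itself, the 2 × 3 interaction has power above 0.999 at both sizes. But f = 0.25 then requires D = 0.5 × 0.25/0.118 = 1.06 SD in the first pattern, and 0.5 × 0.25/0.125 = 1.0 SD for the single contrast. A half-SD difference is about half the size the f value implies.

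**Step 4: sensitivity to r (an assumed range, not from the article).** At 27+27, in the order of the table, power is 0.54, 0.42 and 0.52 at r = 0.6, and 0.45, 0.35 and 0.44 at r = 0.5.

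**Step 5: the condition effect itself.** For a paired 0.5 SD contrast within one group, λ = n×0.25/(2×0.25). Power is 0.942 at n = 27 and 0.963 at n = 30. Pooling the groups raises it further.

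**The case against.** The strongest reply is that nothing practical depends on 15. The trial recruits 30 per group, and 15/0.9 rounds up to only 17. The 3 × 4 interaction calculation misses 80% by one participant, and the condition contrast behind the stated hypothesis (activity against control) is well powered even within one group. Section 2.3.1 also claims no power for the ADHD comparison. All of this stands. It limits the consequence but does not make the sentence correct.

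Three stronger readings are tempting, and the article does not support them.

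- *The ADHD comparison is underpowered at 30+30.* This depends on the effect chosen. At f = 0.25 power exceeds 99%, and in the most favourable 0.5 SD pattern it is 80.5% at 30+30. It falls below 80% at full recruitment only for the graded pattern or the single contrast; the favourable pattern falls below only after the 10% loss.
- *The standardised effects of 0.28 and 0.35 cited in the article are realistic targets for the ADHD interaction.* They are effects of activity on inhibition and on academic outcomes, not differences in effect between children with and without ADHD.
- *The n-back reliability of 0.60–0.80 contradicts r = 0.75.* "The median reliability coefficient alpha for this task in children population ranges" introduces an internal-consistency figure for a secondary outcome. It is not a correlation between sessions a week apart, and the Phase I primary outcome is the P3 component. No figure in the article contradicts 0.75.

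**Conclusion.** The statement is wrong as written, and the error lies in what it describes more than in the number of children. The named interaction does not exist within a child. In its nearest computable form it has 76.5% power at 15, not 80%. The figure 15 belongs to a within-factor effect. The group factor that splits the sample and enters the model is missing, and the f-to-d translation does not carry over to it.

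For a 0.5 SD group difference in the condition effect at r = 0.75, power is 68–80% at 30+30 and about 63–76% at 27+27. These figures rest on sphericity, equal variances, a common correlation and the patterns shown; they fall quickly if r is lower. The sample does not need to change on this ground.

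**What to change.** Keep 30+30. Replace the 15-participant sentence in section 2.3.1 with power at 30+30 and at 27+27 for three effects that the design can estimate:

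- (a) the condition contrast pooled over groups;
- (b) the same contrast within each group;
- (c) condition × group.

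For each, name the effect pattern and the SD difference used. Drop the general equation of f = 0.25 with d = 0.5. Show sensitivity to r, for example 0.5 to 0.75, labelled as an assumption. State that power for condition × group at a 0.5 SD difference is about 63–76% after the stated loss at r = 0.75. Remove the reference to a 3 × 4 within-child interaction.

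The cost is rewording only. No child is added and no procedure changes; the protocol simply becomes more modest about the ADHD comparison.
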